#### Primary outcome measure

##### Star cancellation task (SCT)

The SCT is developed to detect the presence of VSN in the near extra personal space in patients with stroke, and consists of 52 large stars, 13 letters, and 10 short words interspersed with 56 smaller stars [35]. In our study, the SCT will be presented on a laptop screen (screen size: 14 in.). The patient is instructed to mark all targets by touching the screen with the finger (small stars). After each touch, a small circle appears at the touched location and remains on the screen. Two small stars in the center are used for demonstration. To determine the severity of the VSN, quality of search (QoS) for the left and right visual fields will be derived. This score combines speed and accuracy in a single measure, and is calculated using the equation as shown below [36]. A high score reflects a combination of a high number of cancelled targets, and a high cancellation speed.$$QoS=\frac{{N_{cor}}^2}{N_{tar} \cdot {t}_{tot}}$$

Where *N*_*cor*_ is the number of cancelled targets (correct responses), *N*_*tar*_ is the total number of targets, and *t*_*tot*_ is the total time spent.

The SCT, as well as the CVDT and MLBT-d (see subsection “Secondary outcome measures”), will be administered on the same touch screen laptop as will be used for the training (HP EliteBook × 360 1040 G5 Notebook; screen size: 14 in.). PsychoPy will be used to control stimulus presentation and recording of behavioral responses.

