### Patient sample – inclusion and exclusion criteria

Patients with a clinically diagnosed, chronic stroke and with signs of neglect symptoms (based on clinical judgment), will be considered eligible for our study. Patients will be recruited by psychologists of healthcare organizations in The Netherlands that are specialized in supporting and treating people with acquired brain injury (InteraktContour, De Hoogstraat Revalidatie, Heliomare, De Noorderbrug, Esdégé-Reigersdaal). The inclusion of participants started in September 2020 and data will be collected until September 2023.

Inclusion criteria are: 1) neurologically objectified stroke (first or recurrent, ischemic or intracerebral or subarachnoid hemorrhagic lesion; 2) stroke occurred when patient was 18-80 years of age; 3) chronic stroke (> 6 months post-stroke onset); 4) sufficient comprehension and communication skills to benefit from training (based on clinical judgement); and lastly 5) a screening containing four neuropsychological tests will be performed to evaluate the current severity of the neglect, since the diagnosis of neglect may have been established months or even years ago in our sample of chronic stroke patients.

Exclusion criteria are: 1) currently engaging in cognitive rehabilitation treatment or neglect treatment; 2) physically or mentally unable to participate (based on clinical judgment); 3) hemianopsia (based on clinical judgement); 4) severe communicative disability, as task descriptions need to be understood; 5) local scalp injuries; 6) eczema on scalp or psoriasis; 7) diagnosed (neuro) psychiatric or neurodegenerative diseases; 8) current alcohol and/or drug abuse; and 9) pregnancy, due to tACS safety considerations (5-9).

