##### Schenkenberg line bisection task (SLBT)

The SLBT consists of 20 horizontal lines, varying from 10 to 20 cm in length (average 15 cm), at three different positions (left, middle, right) on a landscape-oriented A4 sheet [32]. Patients will be asked to mark their perceived midpoint of every line. The following formula will be used to calculate the relative deviation score:$$deviation=\frac{\left( bisection\ mark- true\ center\right)}{true\ center}\cdot 100\%$$

Where values are always measured from the left end of the line. The relative deviation scores will then be averaged across all 20 lines to generate the summary score, and across the three line positions to generate the left, middle, and right average score, respectively. VSN is indicated when the average bisection mark deviates more than 10% from the true center [32].

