Where dPL and dPR are expressed as a proportion of the endpoint change (40 mm), and range from 0 to 1. Perfect performance would yield symmetrical right and left endpoint weightings of 0.5, and an EWB-value of zero. An EWB-value above zero indicates a greater influence of the right endpoint (over the left), and would be a sign for left sided neglect. To define cut-off scores for the MLBT, we administered the task to healthy controls (*n* = 46, female = 47.7%, age = 57.8 years, SD = 9.2). This yielded a mean EWB of −.0217 (SD = .0546). Scores of 2 SD’s above and below the mean are considered to exceed normal range, leading to upper and lower cut-offs for left and right neglect respectively, of + 0.09 and − 0.13. Study protocol was approved by the ethical committee of the Faculty of Psychology and Neuroscience at Maastricht University (ERCPN number: 177_03_03_2017_S32).

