#### Secondary outcome measures

##### Computerized visual detection task (CVDT)

The CVDT measures perceptual sensitivity and attentional selection in each hemifield [28, 29, 37, 38]. During the task, the patient is seated in front of the laptop screen at 52 cm distance. The patient is asked to fixate on the fixation cross at the center of the screen. Gabor patches (spatial frequency = 1.5 cycles per degree, envelope standard deviation = 7.5°, random orientation) are presented to the left, right and bilateral sides of the screen at 14° eccentricity. Stimuli are shown for 100 ms and stimulus size is 10°. The patient is instructed to indicate the position of the stimulus (left, bilateral, or right) by pressing the <, ˅, or > key, respectively. For each trial, the stimulus position, contrast level, and response are recorded. Video mode is 1280 × 720 at 60 Hz.

For each of the three locations (left, bilateral, right) independently, the contrast of the stimuli is adaptively changed on a trial-by-trial basis. The following parameters are used: prior grating contrast = 1, prior standard deviation = 0.5, beta = 3.5, gamma = 0.01, delta = 0.01, and aim performance = 0.5 (50% detection rate). At the beginning of the task, nine practice trails are presented (i.e. three for each condition; left, bilateral, right) for the patient to become familiar with the task. The stimuli are at maximum contrast, are not part of the staircase procedure, and are not saved. After each practice trial, short written feedback is given (‘Correct’, ‘Wrong’) in the center of the screen. Then, in the actual task, three randomly interleaved staircases are included (left, right, bilateral), with 40 trials each.

Correct hits will be weighted by the contrast level, according to the following formula:$$weighted\ hits=\frac{\log_{10}{contrast}_{max}}{\log_{10}{contrast}_{trial}}$$

Where *contrast*_*max*_ is 100% [29]. This variable accounts for the logarithmic nature of contrast detection, and makes trials count more when the contrast was low. To illustrate, trials detected at maximum contrast receive a score of 1, whereas trials detected at minimal contrast level of 10% receive a score of 2. Performance of the CVDT will be the sum of weighted hits per condition (ipsilesional stimulus, contralesional stimulus, bilateral stimulus), resulting in a score of 0 to 76.49 per condition.

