##### Baking tray task (BTT)

The patient is asked to distribute 16 cubes of 3.5 cm as evenly as possible over a 75 × 100 cm board (as if spreading out buns on a baking tray) [39]. The entire board will be scanned using the Microsoft Lens iOS app. Coordinates of all cubes will be manually identified using a custom Python script. An average positive x-coordinate indicates a rightward bias.

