#### Active tACS

The experimental group will receive active tACS during each session of the VST. To understand how tACS can correct for the attentional bias seen in VSN patients, in the next paragraph we elaborate on the rationale of our study.

Previous electroencephalography studies with healthy participants have linked attention shifts to alpha power in posterior parietal cortices [23–26]. To specify, increased alpha power reflects suppression of incoming sensory information. Thus, shifting attention to the right hemifield is accompanied by alpha power increases in the right hemisphere (inhibiting the unattended left hemifield) and alpha power decreases in the left hemisphere (release from inhibition). Interesting for the field of neglect rehabilitation is that previous studies have shown that tACS can increase the power of the alpha frequency [48, 49]. If indeed alpha power is increased in the ipsilateral relative to the contralateral side of attention, we hypothesize that the bias in visuospatial attention seen in neglect patients can be corrected for by boosting the alpha power in the contralesional parietal cortex by tACS.

Therefore, in the current study a small circular (diameter: 2.1 cm, thickness: 2 mm) and a large (outer diameter: 11 cm; inner diameter: 9 cm, thickness: 2 mm) rubber ring tACS electrode (NeuroConn, Ilmenau, Germany) will be placed onto the contralesional parietal cortex, with the small electrode positioned over P3 or P4 (based on the international 10-20 EEG system) and the large electrode centered around it. This ring electrode montage enables a higher spatial focality as compared to standard rectangular electrodes [50]. TACS ring electrodes will be attached to the patient’s head with conductive gel (ten20 paste, Weaver and Company, Aurora, CO, USA). The conductive gel will be used to reduce the impedance between skin and electrodes to below 10 kΩ.

Stimulation frequency and peak-to-peak intensity will be set to 10 Hz and 1.5 mA, phase offset will be set to 0 and 100 cycles (10s) will be used for ramping up. At the start of the VST, the tACS will be started. When the training is finished, after maximally 40 minutes, the tACS will be switched off.

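### Left- and right-neglect patients can both be enrolled, but the primary outcome and three secondary outcomes are defined by left and right, with no stated recoding to the side of the lesion

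*Protocol article*

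**What the plan says.** **Who can enter.** The inclusion criteria of the Protocol article ask for a "neurologically objectified stroke (first or recurrent, ischemic or intracerebral or subarachnoid hemorrhagic lesion" and set no condition on hemisphere. The MLBT section derives two limits from healthy controls, "leading to upper and lower cut-offs for left and right neglect respectively", namely +0.09 and -0.13. A positive result on any one of four screening tasks is enough to proceed. Under Active tACS the montage is contralesional, "with the small electrode positioned over P3 or P4". Lesion side is recorded as a baseline descriptor.

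**How the outcomes are scored.**
- SCT (primary): "quality of search (QoS) for the left and right visual fields will be derived".
- SLBT (secondary, defined under Screening tasks): a signed percentage deviation. "Where values are always measured from the left end of the line".
- MLBT-d (secondary, defined through the MLBT): the endpoint weightings bias, EWB = dPR - dPL. "An EWB-value above zero indicates a greater influence of the right endpoint (over the left), and would be a sign for left sided neglect".
- BTT (secondary): "An average positive x-coordinate indicates a rightward bias".
- CVDT (secondary), by contrast: "Performance of the CVDT will be the sum of weighted hits per condition (ipsilesional stimulus, contralesional stimulus, bilateral stimulus").

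**How they are analysed.** Statistical analyses specifies linear mixed models with time, group and their interaction. The potential covariates are baseline score, time since stroke, gender and age. No sign reversal, contralesional recoding or lesion-side term is mentioned. The minimization factors are age, gender and previous neglect treatment.

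**The concern.** The group-by-time contrast averages change over patients, so a given change must mean the same thing in every patient. On the three signed scores it does not. A left-neglect patient who improves moves down from a rightward bias, and a right-neglect patient who improves moves up from a leftward bias. Averaged together, the two partly cancel.

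The SCT has a different problem. QoS is not signed, so nothing reverses. But each field is the neglected field for some patients and the intact field for others, so a pooled analysis of either field dilutes the effect. The article also does not say which field, or which contrast of the two, is the primary variable.

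At stake are power in a 22-patient trial and an open choice between left, right and contralesional QoS on the primary outcome. If that choice is made after unblinding, it can follow the data.

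**Working it through.** **1. The plan's own figure.** Sample size estimates gives f = 0.40, 2 groups, 2 sessions, alpha 0.05 and power 0.80, leading to 16 patients. The correlation between sessions is not stated; 0.5 is assumed here.

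- Noncentrality = N × f² × m / (1 - rho) = 16 × 0.16 × 2 / 0.5 = 10.24, with 1 and 14 degrees of freedom. Power is 0.845.
- N = 14 gives 0.785, so 16 is reproduced. With 25% dropout, 16 / 0.75 = 21.3, rounded up to 22.
- The implied group difference in change, in SDs of change, is √(4 × 10.24 / 16) = 1.6.

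This calculation is stated for the CVDT, which is already scored by lesion side. It is borrowed below only as a scale. The protocol states no power for the four outcomes at issue.

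**2. Dilution of the mean.** Let p be the share of right-neglect patients and d the benefit in the affected direction.

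- Signed scores: (1-p)d - pd = (1-2p)d.
- Left-field QoS, if the ipsilesional field shows no effect: (1-p)d + p × 0 = (1-p)d. Pooling the right field would dilute by the share of left-neglect patients instead.

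The article does not give p; 10%, 20% and 30% are assumptions. Replacing f by 0.40(1-2p) or 0.40(1-p) in step 1 gives:

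| p | signed: factor | power, N = 16 | power, N = 22 | left field: factor | power, N = 16 | power, N = 22 |
|---|---|---|---|---|---|---|
| 0 | 1.0 | 0.84 | 0.95 | 1.0 | 0.84 | 0.95 |
| 10% | 0.8 | 0.66 | 0.82 | 0.9 | 0.76 | 0.90 |
| 20% | 0.6 | 0.43 | 0.57 | 0.8 | 0.66 | 0.82 |
| 30% | 0.4 | 0.22 | 0.30 | 0.7 | 0.55 | 0.70 |

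N = 16 is the planned number after dropout; N = 22 assumes that all randomized patients contribute in full.

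**3. Sensitivity to the baseline effect.** If d is instead set so that 8 per arm gives exactly 80% power in a two-sample t-test (d = 1.51), power is 61%, 39% and 20% for signed scores and 71%, 61% and 50% for left-field QoS. The pattern is the same.

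**4. Added variance.** Step 2 changes the mean only. Mixing directions also widens the spread. For signed scores the active-arm variance becomes 1 + 4p(1-p) × 1.6², which at p = 10% is 1 + 0.36 × 2.56 = 1.92. A simulation that includes this (8 per arm, change difference 1.6 SD, no training gain common to both arms) gave power of 0.53, 0.30 and 0.16 for signed scores and 0.71, 0.58 and 0.46 for the left field. In this respect the table is lenient.

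**The case against.** The strongest reply is that the article never says raw left and right scores are pooled.

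- The SCT section derives both fields, which is a necessary step towards a contralesional score. The CVDT also presents left and right stimuli and is then summarised by lesion side.
- The SLBT and EWB sign rules sit under Screening tasks, where a raw sign is needed to diagnose the side of neglect. The BTT sentence only explains an axis.
- The article thinks contralesionally throughout, and a fuller plan that is not shown may recode.
- The power figures rest on an unknown p and on an effect size borrowed from the CVDT.

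Much of this stands. A reader might infer that right-neglect patients will enter the primary analysis through their healthy field. The article does not support that, because it selects neither field. A reader might also infer that the treatment contrast is biased because lesion side is not a minimization factor. That does not follow either: an imbalance in lesion side would be a chance imbalance under random allocation.

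What does not stand is that this is only missing detail. MLBT-d and SLBT are outcomes whose only given definitions are the signed ones. The article states lesion-relative scoring for one secondary outcome and a left/right frame for the primary. Statistical analyses contains nothing that reconciles them. Baseline score as a covariate carries the starting sign but does not reverse the direction of a patient's change.

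**Conclusion.** The concern holds in conditional form. The article admits both sides of neglect, defines SLBT, EWB and BTT with a left/right sign, derives the primary QoS by left and right field, and gives lesion-relative scoring for the CVDT alone. If the scores are modelled as defined, benefit in right-neglect patients counts against treatment on three secondary outcomes, and any single SCT field is the unaffected one for part of the sample.

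The size cannot be fixed from the article. It is zero at p = 0. The left-only Balloons criterion and the communication requirements may keep p low, but neither excludes right neglect. For p of 10% to 30% the mean effect shrinks to 80% to 40% on signed scores and to 90% to 70% on left-field QoS. The second range assumes no effect in the ipsilesional field. That may not hold, because QoS divides by total time and faster overall search could move either field.

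The consequence is lost power plus possible chance imbalance, not systematic bias. Severity is moderate.

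**What to change.** Before unblinding, state in the analysis plan:

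1. SCT QoS is analysed as contralesional and ipsilesional, with contralesional QoS, or one stated contrast of the two, as the single primary variable.
2. SLBT, EWB and BTT are multiplied by -1 for patients with left-hemisphere lesions, so that a positive value always means ipsilesional bias, in line with the CVDT.
3. Because recurrent strokes are eligible, which side counts as the lesion side when there is more than one lesion. The side already used to choose between P3 and P4 would keep scoring and stimulation consistent.
4. The number of left- and right-lesion patients is reported by arm.

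The cost is one recoding step with a variable already collected, plus a few lines of text. No extra patients, visits or measurements are needed. If a fuller plan already recodes in this way, a sentence saying so closes the point.

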#### Secondary outcome measures

##### Computerized visual detection task (CVDT)

The CVDT measures perceptual sensitivity and attentional selection in each hemifield [28, 29, 37, 38]. During the task, the patient is seated in front of the laptop screen at 52 cm distance. The patient is asked to fixate on the fixation cross at the center of the screen. Gabor patches (spatial frequency = 1.5 cycles per degree, envelope standard deviation = 7.5°, random orientation) are presented to the left, right and bilateral sides of the screen at 14° eccentricity. Stimuli are shown for 100 ms and stimulus size is 10°. The patient is instructed to indicate the position of the stimulus (left, bilateral, or right) by pressing the <, ˅, or > key, respectively. For each trial, the stimulus position, contrast level, and response are recorded. Video mode is 1280 × 720 at 60 Hz.

For each of the three locations (left, bilateral, right) independently, the contrast of the stimuli is adaptively changed on a trial-by-trial basis. The following parameters are used: prior grating contrast = 1, prior standard deviation = 0.5, beta = 3.5, gamma = 0.01, delta = 0.01, and aim performance = 0.5 (50% detection rate). At the beginning of the task, nine practice trails are presented (i.e. three for each condition; left, bilateral, right) for the patient to become familiar with the task. The stimuli are at maximum contrast, are not part of the staircase procedure, and are not saved. After each practice trial, short written feedback is given (‘Correct’, ‘Wrong’) in the center of the screen. Then, in the actual task, three randomly interleaved staircases are included (left, right, bilateral), with 40 trials each.

Correct hits will be weighted by the contrast level, according to the following formula:$$weighted\ hits=\frac{\log_{10}{contrast}_{max}}{\log_{10}{contrast}_{trial}}$$

Where *contrast*_*max*_ is 100% [29]. This variable accounts for the logarithmic nature of contrast detection, and makes trials count more when the contrast was low. To illustrate, trials detected at maximum contrast receive a score of 1, whereas trials detected at minimal contrast level of 10% receive a score of 2. Performance of the CVDT will be the sum of weighted hits per condition (ipsilesional stimulus, contralesional stimulus, bilateral stimulus), resulting in a score of 0 to 76.49 per condition.

##### McIntosh line bisection task-digitized (MLBT-d)

A digitized version of the above described MLBT (subsection “Screening tasks”) is also used as study outcome measure. Each of the 32 lines of the MLBT-d are presented individually on a laptop screen. The patient is asked to mark the subjective midpoint of each line by touching the screen with the finger.

##### Schenkenberg line bisection task (SLBT)

In addition to the MLBT(−d), which is still a novel method for administering and analyzing line bisection, we will administer the SLBT, which is a simple line bisection task, widely used in the diagnosis and study of VSN [32]. A description of the SLBT is already given in subsection “Screening tasks”.

##### Baking tray task (BTT)

The patient is asked to distribute 16 cubes of 3.5 cm as evenly as possible over a 75 × 100 cm board (as if spreading out buns on a baking tray) [39]. The entire board will be scanned using the Microsoft Lens iOS app. Coordinates of all cubes will be manually identified using a custom Python script. An average positive x-coordinate indicates a rightward bias.

##### Catherine Bergego scale (CBS)

The CBS is an observation scale for VSN in ADL [40, 41] and will be filled out by a therapist or proxy (partner or caregiver). Neglect severity will be scored for each of 10 items, resulting in a total score of 0 (no neglect) to 30 (severe neglect).

##### Subjective neglect questionnaire (SNQ)

The SNQ is a 19-item questionnaire that will be administered to patients and proxies, asking them to rate the presence of common problems associated with neglect [42]. Each item will be scored on a five-point scale according to the frequency of the occurrence of the difficulty (ranging from at most once a month to at least once a day). The minimum score of 19 indicates no reported problems, the maximum score is 95 [18].

#### Baseline descriptors

The following data will be collected: demographics (age, gender, handedness, educational level), stroke characteristics (time post-stroke, lesion side, stroke type (ischemic, intracerebral or subarachnoid haemorrhage) and stroke history (first-ever or recurrent)), and global cognitive functioning (Montreal Cognitive Assessment; MoCA version 8.1 [43]).

### Randomization, blinding and treatment allocation

Participants will be randomly assigned to either the active tACS plus VST group *or* the sham tACS plus VST group. We will apply minimization, a method of adaptive stratified sampling, to prevent imbalances of potential confounders between the active and sham group. This will be achieved using “MinimPy”, an open-source customizable minimization program for allocation of patients to parallel groups in clinical trials [44]. Patients will be stratified according to the following factors: age (18-59/60-80), gender (male/female), and having had previous neglect treatment (yes/no). The software will automatically send an e-mail with the randomization results to a not-closely involved and only un-blinded research assistant. This assistant will then pick a 5-digit code from the list of codes provided in the NeuroConn DC Stimulator user manual (neuroConn GMBH) that either initiates the preprogrammed active stimulation protocol or the sham protocol. The un-blinded assistant will assign this unique code to the enrolled patient in question and will send the code to the blinded researchers. The un-blinded assistant will further not be involved in the study, so will play no further role in inclusion, testing or analyses. The blinded researchers will perform the intervention and administer the outcome measurements, independently of the un-blinded assistant.

Patients will also be blinded to treatment allocation.

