In our study, we will compare the CVDT test score before and after the six-week training period. To calculate the required sample size of our study population, we made use of G*Power (version 3.1) [58]. To find an effect size of d = .80 (Cohen’s f = .40), we calculated parameters for a repeated measures ANOVA with a 2 × 2 design (within-between interaction, 2 groups, and 2 testing sessions), a power of 0.80 and an alpha of .05, which yielded a total required sample size of 16 patients (8 per group). This is a conservative estimate, as mixed linear modeling, the method we will use to analyze our data, is more powerful than repeated measures ANOVA [59]. We choose to set this to 22 patients (11 per group) because patients may dropout due to the relatively long training period of 6 weeks (dropout estimated at 25%). The abovementioned RCT’s included a comparable number of patients per group (approximately 10 per group) and reported significant effects and large effect sizes, so we too expect that our design will have sufficient power, which we confirm with our a priori sample size calculation.

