### Statistical analyses

The background characteristics of the patients will be described by using descriptive statistics. Baseline characteristics of the intervention and control group will be compared to detect differences at the start of the trial. Linear mixed model regression analyses with random effects for intercept and slope will be used to test for change in the primary and secondary outcome measures both within and between group. The predictors of theoretical interest are the effects of time and group and the interaction between time and group (fixed effects). Baseline score of the outcome measure, time since stroke, gender, and age will be introduced as potential fixed covariates. This is regardless whether or not these variables differ between groups, to enhance the fit of the model. Post-hoc contrasts will be performed for the interaction between time and group to test differences in treatment effects by intervention group allocation. The intention-to-treat principle is used by including all patients as randomized in the analyses, regardless of whether they received the complete program (dropout, non-adherence). Significance is set to *p* < .05 (two-sided). Analyses will be performed in IBM SPSS Statistics version 26.

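### Previous neglect treatment is a minimisation factor but not an analysis covariate; if it predicts change in the outcome, the treatment test is somewhat conservative and loses power

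*Protocol article*

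**What the plan says.** Under Randomization, blinding and treatment allocation, the protocol article names three minimisation factors: age in two bands (18-59 and 60-80), "gender (male/female), and having had previous neglect treatment (yes/no"). The stated purpose is "to prevent imbalances of potential confounders between the active and sham group".

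Under Statistical analyses, the model is described as follows: "Linear mixed model regression analyses with random effects for intercept and slope will be used". The covariate list reads: "Baseline score of the outcome measure, time since stroke, gender, and age will be introduced as potential fixed covariates". The next sentence says that these enter whether or not the groups differ on them, so as to improve model fit. The treatment effect is tested through the interaction: "Post-hoc contrasts will be performed for the interaction between time and group to test differences in treatment effects by intervention group allocation".

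Age and gender therefore pass from the allocation scheme to the model. Previous neglect treatment does not. Time since stroke, which is not an allocation factor, is included.

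**The concern.** Balancing the arms on a prognostic factor lowers the true variance of the treatment estimate. If the factor is then left out of the model, its variance stays in the residual. The reported standard error is larger than the real one, the confidence interval is too wide and the test rejects less often than its nominal level.

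The article's own reasoning points towards inclusion. It treats the three factors as potential confounders, and it adds covariates to improve fit regardless of imbalance. A link with outcome is also plausible: both arms receive visual scanning training, the current conventional treatment, so earlier neglect treatment could affect how much a patient still gains. With 22 patients and 25% expected dropout, there is little power to give away.

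**Working it through.** **1. The plan's own figure.** The sample size section states "To find an effect size of d = .80 (Cohen’s f = .40"), a 2 × 2 within-between interaction, power 0.80 and alpha 0.05, giving N = 16. With λ = f²·N·m/(1 − ρ), m = 2 and ρ = 0.5 (ρ is not stated and is assumed here), λ = 0.16 × 16 × 2 / 0.5 = 10.24 on 1 and 14 degrees of freedom, and power is 0.845. At N = 14 it is 0.785. So 16 reproduces, and 16/(1 − 0.25) = 21.3 rounds up to 22. The omitted factor does not affect this calculation.

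**2. Expected size under exact balance.** Let the factor be split 50/50 with effect β in residual SD units. Omitting it raises the residual variance from 1 to about 1 + β²/4, while the true variance of the treatment estimate is unchanged. The standard error is then overstated by √(1 + β²/4):
- β = 0.5: √1.0625 = 1.03
- β = 1.0: √1.25 = 1.12
- β = 1.5: √1.5625 = 1.25

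Minimisation on three factors does not balance exactly, so a simulation is needed.

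**3. ANCOVA-type simulation.** N = 22, with deterministic minimisation on age group, gender and previous treatment. The follow-up score is regressed on group, baseline, time since stroke, age and gender, with and without previous treatment; 4,000 runs per scenario. The effect sizes, the 50% prevalence and the allocation probability are assumptions. Power is for a group difference of 0.8 residual SD.

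| Factor effect (SD) | SE ratio, omitted | Type I, omitted | Type I, included | Power, omitted | Power, included |
|---|---|---|---|---|---|
| 0 | 1.01 | 0.043 | 0.045 | 0.37 | 0.37 |
| 0.5 | 1.05 | 0.041 | 0.045 | 0.35 | 0.36 |
| 1.0 | 1.11 | 0.033 | 0.049 | 0.31 | 0.38 |
| 1.5 | 1.17 | 0.024 | 0.053 | 0.22 | 0.38 |

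The SE ratio is the model standard error divided by the true SD of the estimate. The Monte Carlo error of a type I estimate is about √(0.05 × 0.95/4000) = 0.003. The power columns compare omission with inclusion; they are on a different effect scale from the plan's 0.80 and do not judge it.

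With an 80% biased coin, type I error with the factor omitted is 0.042 at 0.5 SD and 0.037 at 1.0 SD. With 16 patients under deterministic minimisation it is 0.044, 0.036 and 0.026 at 0.5, 1.0 and 1.5 SD.

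**4. The planned time-by-group contrast.** If baseline (T0) stays in the response, the T3 contrast compares the arms on Y(T3) − Y(T0). A stable shift βF appears in both terms and cancels. Only an effect of the factor on change survives, and a main effect cannot remove that.

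A check used six visits with categorical time, 22 patients, a random intercept only, and previous treatment in 5 of 11 and 6 of 11 patients per arm; 30 runs per scenario. Standard error of group × T3:

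| Factor acts on | Omitted | Main effect added | Factor × time added |
|---|---|---|---|
| Level only (1 unit) | 0.420 | 0.420 | 0.421 |
| Change from T3 on (1 unit) | 0.459 | 0.459 | 0.426 |
| Both | 0.450 | 0.450 | 0.416 |

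In the second row the factor-by-time term lowers the standard error by (0.459 − 0.426)/0.459 = 7%. The main effect does nothing in any row.

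**The case against.** The sponsor could fairly say that nothing shows previous treatment to be prognostic once baseline score, age, gender and time since stroke are in the model. That stands. The article speaks only of potential confounders, and its Background says it is unclear why some patients benefit from scanning training. A reader might infer that the standard errors are simply too large, or that previous treatment is the factor most closely tied to remaining gain. The documents support neither.

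A reader might also take larger figures from a plain two-arm comparison of 10 per arm with one exactly balanced factor, where type I error falls to 0.038, 0.028 and 0.019 if the factor explains 10%, 20% or 30% of outcome variance. Those figures leave out the repeated measures, the baseline score and the other covariates, and the range excludes a null or weak factor. They do not describe the planned contrast.

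At 0.5 SD the effect is small: 0.041 against 0.043 with no factor effect is within Monte Carlo error. For a contrast on change, a factor that shifts only the level costs nothing.

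Finally, a condensed article may leave the final covariate set to an analysis plan that is not shown. But this article prints a list that takes two of the three allocation factors, adds one that is not an allocation factor, and gives no reason for the gap. The mismatch is in what is stated, so it can be raised.

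**Conclusion.** The mismatch is real: one of three minimisation factors is absent from the listed covariates. Its consequence is conditional. If previous neglect treatment predicts change in the outcome beyond the listed covariates, the standard error of the treatment contrast is somewhat too large and the test conservative.

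Under the ANCOVA-type assumptions at N = 22, the standard error is overstated by about 5%, 11% and 17% for factor effects of 0.5, 1.0 and 1.5 SD. At 1.0 SD, power for a 0.8 SD difference is 0.31 with the factor omitted and 0.38 with it included. If the factor is not prognostic, omission does no harm. Neither bias nor a raised false-positive rate follows.

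The results rest on assumed effect sizes, a 50% prevalence and an assumed allocation probability. The mixed-model check had few runs and no random slope, so it shows the mechanism better than the exact size. This is a modest and inexpensive improvement to the analysis, not a threat to the trial's validity.

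**What to change.** Add previous neglect treatment (yes/no) to the covariates of the primary and secondary models, in a form that reaches the treatment contrast, and state whether T0 is part of the response. The article lists the baseline score as a covariate but does not say this.

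- **Post-baseline response only, baseline score as covariate:** enter the factor as a fixed covariate. Cost: one degree of freedom.
- **T0 kept in the response:** enter the factor with its interaction with time. Cost beyond the main effect: up to 6 − 1 = 5 terms for outcomes measured at six visits with categorical time, and 4 − 1 = 3 for the daily-living measures taken at four visits. In 22 patients this is not negligible, which favours the first form.

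Adding a main effect while T0 stays in the response would look like a correction but leave the contrast as it is. If the sponsor prefers to leave the factor out, the reason should be stated. No new data are needed, since the factor is recorded for minimisation.
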